In this paper, we describe a study protocol for a stepped-wedge randomized controlled trial (SW-RCT) stemming from a state-academic partnership that will test a multicomponent, clinic-level intervention, called Coaching for Addiction Recovery Enhancement (CARE). We will test whether CARE improves treatment process quality and recovery outcomes over treatment as usual, particularly for OUD. The SW-RCT design was selected mainly because the intervention is conducted at the clinic-level and, from a resource perspective, it would be impractical to provide the intervention to all clinics at once given the facilitation model being utilized. Further, the stepped-wedge design was seen as more acceptable and ethical for key program stakeholders (notably the single state agency that regulates SUD treatment [SSA]) due to the potential benefits from the resources being provided as part of the intervention package (e.g., training support from the SSA) compared to a parallel randomization design. The CARE intervention includes the following components: (1) staff clinical training and tools, (2) quality improvement and change management training, (3) external facilitation to support implementation and sustainability of quality improvement, and (4) the eTPA8 client-reported treatment progress tool to support data-driven decision making and clinic-level quality measurement. See Fig. 1 for our intervention conceptual model. We describe intervention components in more detail in the method section. Study aims and hypotheses are the following:
Aim 1: Test the effect of CARE on treatment process quality measures and recovery outcomes.
Hypothesis 1: CARE will improve clinic-level rates of treatment process quality measures (i.e., initiation of and adherence to OUD medications, in-treatment symptom and therapeutic progress, 6-month treatment retention) and recovery outcomes (i.e., substance use, overdoses, self-reported health status, hepatitis C infection [HCV], and emergency department [ED] visits).Aim 2: Examine association of changes in the eTPA8 client-reported treatment progress tool with treatment retention and substance use outcomes.

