Hypothesis 2: Positive change in the eTPA8 scale will be associated with longer retention and reduced substance use at follow-up.Aim 3: Examine whether there are program admission changes in terms of client complexity (e.g., homelessness, psychiatric conditions) to test impact on client access (i.e., adverse selection) as clinics monitor quality measures.
Hypothesis 3: Clinic rates of severe OUD (i.e., daily use and/or injection use), homelessness and psychiatric conditions at admission during the year following the CARE intervention will decrease from baseline rates.Aim 4: Examine staff attitudes, experiences, and behaviors related to (1) implementing the eTPA8 and clinical practice change, and (2) working with external facilitators to implement QI processes.Aim 5: Estimate addiction program and state intervention costs of CARE and impact on Medicaid costs.

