Two additional data sources will represent client-reported outcomes. First, the 8-item eTPA8 will be completed by clients in participating clinics every 2 weeks; data will be retained in the eTPA8 database for analysis. Second, a sample of 40 clients from each clinic will be recruited to complete a survey: 20 clients at the beginning of the intervention and another 20 6 months after the intervention start date at their clinic. Each participant will be assessed three times: (1) at treatment entry, (2) 3 months post-entry, and (3) 6 months post-entry. We will use a mobile platform to collect this data. To recruit clients, clinic staff will present a recruitment flyer to randomly selected newly admitted clients with a primary or secondary OUD diagnosis. The flyer will describe the study and provide a number where they can text to participate. Participants will digitally consent and complete the baseline assessment on their mobile phone. If they do not complete the assessment, they will be sent reminder text messages at 3 and 7 days. Clients will receive a text message with a link to the assessment at each follow-up point, as well as text reminders if they do not complete the follow-ups. Clients will be compensated with a $20 gift card for each assessment.

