#### Measures

Based on treatment episode and client admission information in the CDS and claims information in Medicaid, clinic level covariates, quality, and outcomes data will be computed in 6-month assessment windows. Client level covariates from the CDS will include frequency of use, injection drug use, age, gender, race/ethnicity, education, residential stability/homelessness, and psychiatric comorbidities at admission. Medicaid claims will be used to identify OUD medications, various health conditions based on ICD-10 diagnosis fields; healthcare episodes based on procedure, rate and NDC codes; and cost based on Medicaid payments for claims and encounters. Clinic rates of 6-month retention will be computed from admission and discharge dates in the CDS. OUD medication initiation and adherence will use data from Medicaid pharmacy claims during an episode. Initiation will be a new OUD medication pharmacy claim within 30 days and adherence will be computed using the NQF 3175 definition [51–53]. Overdoses will be identified by CDC defined combinations of diagnoses and acute care procedure codes [54, 55]. All-cause ED visits will be defined by procedure and rate codes. HCV infections will be defined by diagnoses during any hospitalizations or on two outpatient claims [56, 57]. Costs of healthcare services will be drawn from Medicaid claims and encounter data.

Provider-level covariates will also be calculated. SUD program characteristics will be drawn from computing provider-level statistics from claims as well as from state databases that contain addresses, affiliations, and licensing information. Provider variables will include geographical location, annual census, and hospital affiliation. Geographical information of provider location will be drawn from the Area Health Resources File: poverty, population density, ethnic/racial population, and health professional availability.

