Client-reported treatment process improvement will be computed from change scores on the eTPA8 from baseline to latest administration. Further, the client-self reported mobile survey will include the following measures: (1) past 2-week use of opioids and other substances based on the Addiction Severity Index (ASI) [58], (2) substance use consequences based on the Short Inventory of Problems-Revised (SIP-R) [59], (3) health-related quality of life based on the first item of the SF-36 [60], (4) functional outcomes using the Treatment Effectiveness Assessment [61], past 30-day employment, incarceration, housing status based on the ASI, (5) a visual analog scale measuring cravings to use substances [62], and (6) demographics.

Staff surveys will include measures on practice change capacity (i.e., the change process capability questionnaire) [63, 64], the Opinions About MAT Survey [65], knowledge and perceptions about person-centered care and shared-decision making, and use of data and quality metrics. An interview guide for staff qualitative interviews will be created to reflect the dimensions of the i-PARIHS model (e.g., inner context) [66].

The marginal cost of the CARE intervention will be estimated to inform future intervention development and implementation. We will collect detailed data on staffing and other resources to inform micro-costing computations and estimates of the marginal costs of deploying CARE under real-world conditions [67–69]. Cost data collection will follow generally accepted practice in cost-effectiveness research [67, 68]. In addition, the cost collection procedures and estimations will borrow from methods derived from process engineering [70] and managerial accounting [71–74]. Input prices (i.e., cost of each unit of resource input) will be derived from market rates when available, program budgets, or government pricing schedules (e.g., Bureau of Labor Statistics data on personnel costs for the Northeast region). The first step in the cost tracking will entail developing detailed process maps in conjunction with intervention developers and clinicians to identify all key processes [75]. The cost tracking system will track resources used to deliver the intervention as well as identify research protocol driven costs that would not be part of a real-world implementation [76]. The cost tracking system will identify intervention development costs as well as operational costs associated with running the intervention.

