### Analysis and power

The primary aim of this study is to test whether CARE is associated with greater use of pharmacotherapy for OUD, longer retention in care, and improved recovery outcomes (e.g., reduced drug use). We will employ multiple convergent analytical methods to (a) examine CARE implementation and (b) test association between CARE and OUD treatment outcomes. Analyses will begin with examination of distributions of variables and transformations where appropriate, examination of patterns of missingness, and application of formal imputation methods [77–79] if deemed essential to project aims. Analyses for Aims 1, 2, and 3 will utilize general linear mixed models (GLMM) for stepped-wedge designs [80–85]. For example, to test the effect of CARE on treatment process quality measures (i.e., initiation and adherence to OUD medications, in-treatment symptom and therapeutic progress, 6-month treatment retention) and recovery outcomes (substance use, overdoses, self-reported health status, HCV infection, and ED visits), we will employ stacked difference-in-difference models that test for within and across clinic changes while adjusting for secular trends across time [80, 86, 87]. The models will take the form: *Y*_*ikt*_ = *μ* + *X*_*kt*_*θ* + *β*_*t*_ + *Z*_*ikt*_ + *α*_*k*_ + *e*_*ikt*_, where *β*_*t*_ is a fixed effect for time, *Z*_*ijk*_ is a matrix of covariates measuring individual, geographical, and clinic characteristics for person *i* in clinic *k* at time *t, X*_*kt*_ is an indicator for intervention in clinic *k* at time *t* (coded 0 for baseline then 1 from when intervention begins in clinic through end of study), and *θ* is the treatment effect. *Y*_ikt_ represents a matrix of binary variables: treatment process quality measures (i.e., pharmacotherapy initiation and adherence, in-treatment symptom and therapeutic progress, treatment retention) and recovery outcomes (i.e., substance use, overdoses, self-reported status, HCV infection, and ED visits). We will estimate the effect of CARE (*θ*) while controlling for secular trends (*β*) and adjusting for clustering within clinic (*α*_*k*_) using robust standard errors. We will also conduct a set of falsification tests. These will include (1) testing for variation in program and client characteristics across time of enrollment; (2) examination of variation across study time in the study outcomes for clinics not participating in the study; and (3) examination of variation in intervention effect based on clinics’ baseline levels of quality measures (e.g., comparing top third to bottom third in quality of care at baseline).

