To estimate study power for select outcomes, we drew from methods developed by Hussey and Hughes [80] as implemented in a Stata command, stepped wedge [98]. Using administrative data to estimate sample sizes and baseline rates (μ), we computed detectable differences for a β = 0.80, α = 0.01, ICC/ρ = 0.20, and SW-RCT with 6 crossover points, and 5 clinics randomized at each point. For 6-month retention, assuming step samples sizes (*m*_k_) of 132 and base rate (μ) of 25%, we will be able to find a 2.8pp change in retention (i.e., 27.8%) to be statistically significant and clinically meaningful. We also conducted sensitivity analyses varying ρ (0.10–0.30) and β (0.90) and found detectable differences ranging from 2.6 to 3.2%. For OUD medication initiation, we assume *m*_k_ = 40 Medicaid clients with OUD, μ = 0.40, and find a detectable difference of 6.7%. For ED visits, we assume *m*_k_ = 79 Medicaid clients and μ = 0.40, and find a detectable difference of 3.9%. Consequently, with 30 clinics and 6 steps in our SW-RCT, we will have power to detect moderate and clinically meaningful differences in outcomes.

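### The article's only eTPA8 change score runs to the client's last administration; if it serves Aim 2, its window is set by retention, the outcome it is meant to explain

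*Protocol article*

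**What the plan says.** Aim 2, set out at the end of the Background section, is to "Examine association of changes in the eTPA8 client-reported treatment progress tool with treatment retention and substance use outcomes". Hypothesis 2 gives the direction: "Positive change in the eTPA8 scale will be associated with longer retention and reduced substance use at follow-up".

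The Measures section holds the only definition of eTPA8 change in the article: "Client-reported treatment process improvement will be computed from change scores on the eTPA8 from baseline to latest administration". It fixes no time point for the second score.

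The schedule is under Data sources: "the 8-item eTPA8 will be completed by clients in participating clinics every 2 weeks". Hypothesis 1 describes the construct as an in-treatment one and lists it beside retention ("in-treatment symptom and therapeutic progress, 6-month treatment retention"). Retention itself comes from dates: "Clinic rates of 6-month retention will be computed from admission and discharge dates in the CDS".

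On the model, Analysis and power says: "Analyses for Aims 1, 2, and 3 will utilize general linear mixed models (GLMM) for stepped-wedge designs". The equation that follows is written for the effect of CARE. Its time term is a fixed effect for secular trend, not for time since a client's admission.

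**The concern.** A score that is collected while clients are in treatment stops when they leave. The last score therefore falls close to discharge, and the interval over which change is measured is nearly the same quantity as retention. If clients improve on average as treatment goes on, those who stay longer show more change simply because they were measured later. Length of stay then drives the change score, whereas Hypothesis 2 is of interest because improvement might go with staying.

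At stake is how the retention result of Aim 2 can be read. The trial gives the eTPA8 to clinics for clinical decisions and quality improvement. A positive association with retention would look like support for that use, yet part or all of it could come from the definition.

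**Working it through.** **Inputs from the article.** Scores every 2 weeks (Data sources); change from baseline to the last score (Measures); retention from admission and discharge dates (Measures); 6-month retention of 25% in the power calculation ("base rate (μ) of 25", in per cent). The article states no figure for the Aim 2 analysis, so there is none to reproduce.

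**Window length.** A client retained 26 weeks has 26/2 = 13 post-baseline scores. One who leaves at week 4 has 4/2 = 2.

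**Why an association arises.** Let T be the discharge time, L the week of the last score up to week 26 (L = 2 × floor(min(T, 26)/2)), and s the client's weekly improvement, independent of T. Then

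change = s × L + measurement error, so E(change | T) = mean(s) × L.

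The covariance of change with weeks retained has the sign of mean(s): positive if scores improve on average, zero if they do not move, negative if they worsen. At 0.03 SD per week the expected change is 0.03 × 26 = 0.78 SD for a client who stays 26 weeks and 0.03 × 4 = 0.12 SD for one who leaves at week 4. If all improvement has occurred by the first follow-up score, every client with a change score has the same expected change and the covariance is zero.

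**Size, first set-up.** Assumptions not in the article: exponential discharge, slope SD 0.05 per week, measurement SD 0.5. Discharge is independent of slope. For the plateau rows the same 0.78 SD mean improvement is reached by the week shown and then stops. Repeated runs differed by about 0.01.

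| Mean course | Correlation of change with weeks retained |
|---|---|
| No mean change | 0.00 |
| 0.005 SD/week | 0.04 |
| 0.01 SD/week | 0.08 |
| 0.03 SD/week | 0.23 to 0.24 |
| 0.03 SD/week, measurement SD 1.0 | 0.16 |
| Plateau by week 2 | 0.00 |
| Plateau by week 4 | 0.04 to 0.05 |
| Plateau by week 8 | 0.11 to 0.12 |
| Decline of 0.03 SD/week | −0.23 to −0.24 |

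At 0.03 SD per week, 6-month retention is 46% in the top quarter of change and 26% in the bottom quarter. At 0.01 it is 39% against 33%.

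**Size, second set-up.** Same discharge model; measurement SD 1, slope SD 0.5 over 26 weeks, 1000 runs. Change is compared between clients retained and not retained at 26 weeks by a t-test at two-sided 5%. Both sample sizes are illustrative; 2000 is close to the clinics' yearly number of clients with OUD.

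| Mean improvement by week 26 | Course | Difference in change | False positives, n = 600 | n = 2000 |
|---|---|---|---|---|
| 0 | linear | 0.00 | 6% | 6% |
| 0.25 | linear | +0.15 | 19% | 49% |
| 0.5 | linear | +0.30 | 59% | 97% |
| 1.0 | linear | +0.59 | 99% | 100% |
| 0.25 | early plateau | +0.07 | 6% | 15% |
| 0.5 | early plateau | +0.14 | 16% | 44% |
| 1.0 | early plateau | +0.27 | 45% | 94% |

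**Same check with a common time point.** With change taken at week 4 among clients still in treatment, the first set-up at 0.03 SD per week gives a correlation of 0.00 and 31% retained in both the top and bottom quarters. This agrees with 0.25^(22/26) = 0.31 for retention to week 26 given presence at week 4. In the second set-up false positives stay at about 4% to 6% in every scenario.

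**The case against.** The link to Aim 2 is an inference. The sentence in Measures defines client-reported process improvement, which matches the in-treatment progress outcome of Aim 1, while Aim 2 speaks only of change in the scale. This stands as a limit on certainty. It does not remove the point, because the article offers no other definition.

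The article is a condensed account, and the full protocol or analysis plan may set a landmark, a time-varying term or another model for Aim 2. That is fair, and the absence of such detail here is not the criticism. The criticism is of a definition that is stated and that a later plan would have to replace. The model named for Aims 1 to 3 does not repair it, since its time effect concerns secular trend.

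Three stronger readings are tempting, and the documents do not support them:
- *The analysis would find a positive association under the null.* It may. The article gives no eTPA8 course, and the artefact is small if improvement is slow or early and negative if scores fall.
- *The artefact disappears only if mean change is zero.* It also disappears if improvement is complete by the first follow-up score.
- *Hypothesis 2 as a whole can be confirmed by construction.* Only the retention half was examined. Self-reported substance use comes from surveys at fixed times, 3 and 6 months after entry, and was not simulated.

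Aim 2 is an association aim and not the primary one. The randomised comparison of retention between CARE and usual treatment is not touched by this point.

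**Conclusion.** The point holds in limited form. The one stated definition of eTPA8 change ends at a time set by the client's stay, so using it for the retention half of Hypothesis 2 may produce a positive association that says nothing about improvement as a signal. The condition is that mean scores keep improving after the first follow-up score, which is what one would hope for in treatment but which the article does not document.

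The size runs from negligible to large: in the improving scenarios examined, correlations from 0.00 to 0.24, and false-positive rates from 6% to 99% at n = 600 and from 15% to 100% at n = 2000. These figures rest on assumed trajectories, exponential discharge, and independence of improvement and discharge. Only the 25% retention rate and the 2-week schedule come from the article. The definition should be changed before Aim 2 is analysed; confidence is moderate because the link to Aim 2 is inferred.

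**What to change.** State which analysis the baseline-to-last-score definition serves, and give the retention analysis of Aim 2 its own predictor. Either:
- define change from baseline to a fixed early administration (week 4, for example, with another early time as sensitivity) among clients still in treatment then, and count retention from that landmark; or
- use the current eTPA8 score as a time-varying covariate in a time-to-discharge model.

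Neither option needs new data, since the biweekly scores are kept in the eTPA8 database. The landmark option excludes clients discharged before it. Under the exponential model with 25% retained at 26 weeks, 1 − 0.25^(4/26) = 19% leave before week 4. Against that, 1 − 0.25^(2/26) = 10% leave before week 2 and have no change score under the stated definition either.

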### Analysis and power

The primary aim of this study is to test whether CARE is associated with greater use of pharmacotherapy for OUD, longer retention in care, and improved recovery outcomes (e.g., reduced drug use). We will employ multiple convergent analytical methods to (a) examine CARE implementation and (b) test association between CARE and OUD treatment outcomes. Analyses will begin with examination of distributions of variables and transformations where appropriate, examination of patterns of missingness, and application of formal imputation methods [77–79] if deemed essential to project aims. Analyses for Aims 1, 2, and 3 will utilize general linear mixed models (GLMM) for stepped-wedge designs [80–85]. For example, to test the effect of CARE on treatment process quality measures (i.e., initiation and adherence to OUD medications, in-treatment symptom and therapeutic progress, 6-month treatment retention) and recovery outcomes (substance use, overdoses, self-reported health status, HCV infection, and ED visits), we will employ stacked difference-in-difference models that test for within and across clinic changes while adjusting for secular trends across time [80, 86, 87]. The models will take the form: *Y*_*ikt*_ = *μ* + *X*_*kt*_*θ* + *β*_*t*_ + *Z*_*ikt*_ + *α*_*k*_ + *e*_*ikt*_, where *β*_*t*_ is a fixed effect for time, *Z*_*ijk*_ is a matrix of covariates measuring individual, geographical, and clinic characteristics for person *i* in clinic *k* at time *t, X*_*kt*_ is an indicator for intervention in clinic *k* at time *t* (coded 0 for baseline then 1 from when intervention begins in clinic through end of study), and *θ* is the treatment effect. *Y*_ikt_ represents a matrix of binary variables: treatment process quality measures (i.e., pharmacotherapy initiation and adherence, in-treatment symptom and therapeutic progress, treatment retention) and recovery outcomes (i.e., substance use, overdoses, self-reported status, HCV infection, and ED visits). We will estimate the effect of CARE (*θ*) while controlling for secular trends (*β*) and adjusting for clustering within clinic (*α*_*k*_) using robust standard errors. We will also conduct a set of falsification tests. These will include (1) testing for variation in program and client characteristics across time of enrollment; (2) examination of variation across study time in the study outcomes for clinics not participating in the study; and (3) examination of variation in intervention effect based on clinics’ baseline levels of quality measures (e.g., comparing top third to bottom third in quality of care at baseline).

To examine Aim 4, we will use a concurrent triangulation mixed-methods design such that staff quantitative and qualitative data collection will occur concurrently and results will be integrated after analysis of each [88]. The semi-structured interviews will be transcribed and analyzed using conventional qualitative content analysis [89] following the process outlined in Erlingsson and Brysiewicz [90]. Atlas.ti will be used to manage the data. A codebook will initially be created based on i-PARIHS constructs and will be modified and amended as coding and analysis continues. For the quantitative results, multilevel modeling will be used to examine change over time in survey scores given the nested structure of the data (staff nested within clinics) [91].

For Aim 5, the cost analysis will focus on the provider and state agency perspective as the main decision-maker; consequently, other societal costs are not included in this preliminary analysis. Decision analytical models will be created using measures of central tendency (e.g., means, medians) of observed resource inputs as well as measured estimates of variances for sensitivity analyses. Using TreeAge Pro [92], we will estimate average costs as well as confidence intervals based on simulations drawing from variances of model inputs. We will conduct a series of one-way and two-way sensitivity analyses across model inputs to determine the impact of variability of individual model parameters. Additionally, we will use Monte Carlo simulation to build confidence intervals over which the cost of the intervention may vary. Costs will be presented as ratios: per clinic, per participant, and per unit of each quality measure.

We will also examine the association between CARE and total Medicaid costs. Costs will be modeled using generalized gamma models (GGM), which offer flexibility in modeling non-Gaussian outcomes by computing three parameters to fit the observed distribution: location, scale, and shape [93, 94]. One advantage of GGM is that it is not subject to the retransformation bias stemming from heteroscedasticity in the log-scale often associated with the more common OLS regression on log-transformed healthcare costs [94–96]. We will consider other GLM approaches to analyzing costs and subject these to goodness of fit tests as outlined by Manning [97].

To estimate study power for select outcomes, we drew from methods developed by Hussey and Hughes [80] as implemented in a Stata command, stepped wedge [98]. Using administrative data to estimate sample sizes and baseline rates (μ), we computed detectable differences for a β = 0.80, α = 0.01, ICC/ρ = 0.20, and SW-RCT with 6 crossover points, and 5 clinics randomized at each point. For 6-month retention, assuming step samples sizes (*m*_k_) of 132 and base rate (μ) of 25%, we will be able to find a 2.8pp change in retention (i.e., 27.8%) to be statistically significant and clinically meaningful. We also conducted sensitivity analyses varying ρ (0.10–0.30) and β (0.90) and found detectable differences ranging from 2.6 to 3.2%. For OUD medication initiation, we assume *m*_k_ = 40 Medicaid clients with OUD, μ = 0.40, and find a detectable difference of 6.7%. For ED visits, we assume *m*_k_ = 79 Medicaid clients and μ = 0.40, and find a detectable difference of 3.9%. Consequently, with 30 clinics and 6 steps in our SW-RCT, we will have power to detect moderate and clinically meaningful differences in outcomes.

